**Figure 3 figure3:**
[figure not shown]
Sample of game elements used in the gamified task. (A) Smiling (left) and frowning (right) emoticons received during practice trials for correct and incorrect responses, respectively. (B) Badge earned at the end of the first training session. (C) Progress bar representing proportion of trials completed in each block and a written indicator reflecting the number of blocks completed.

### Outcomes and Measures

#### Overview

Tasks will be presented using Inquisit 6.4 on participants’ internet-connected computers, and questionnaires will be administered using the web-based system Qualtrics (Provo), except for self-reported engagement, which will be administered using Inquisit 6.4. Assessments for all training conditions will be conducted at baseline, during training, immediately after training, and at the 1-month follow-up. A list of all outcomes, measurement instruments, and corresponding time points is presented in Table 1.

**Table 1 table1:** Study outcome measures by assessment time point.

Outcome and variable		Measure	Assessment time point			
			Baseline	During training	Posttraining	1-month follow-up
**Baseline data**						
	Eligibility screening	Self-report questions	✓			
	Demographic information	Self-report questions	✓			
	**Pain experience information**					
		Self-report questions	✓			
		GCPS^a^	✓			
**Primary outcomes**						
	Pain intensity	PROMIS^b^ Pain Intensity 3a	✓		✓	✓
	Pain interference	PROMIS Pain Interference 8a	✓		✓	✓
	**Self-report engagement**					
		1 self-report question		✓	✓	
		IMI^c^ (interest and enjoyment)			✓	
	**Behavioral engagement**					
		Intervention attrition rates		✓	✓	
		Completion rates		✓	✓	
**Secondary outcomes**						
	Attentional bias	Dot-probe task	✓		✓	
	Anxiety	PROMIS Anxiety 8a	✓		✓	✓
	Depression	PROMIS Depression 8b	✓		✓	✓
	Perceived improvement	PGIC^d^			✓	✓
	Interpretation bias	Interpretation bias task	✓		✓	
**Additional measures**						
	Attentional control	ACS^e^	✓		✓	
	Personality characteristics	BIS and BAS^f^ scales	✓			
	Pain-related worrying	PCS^g^	✓			
	Pain-treatment information	Self-report questions			✓	✓
	Validity check	Instructional question	✓		✓	✓
	Manipulation check	1 self-report question			✓	

^a^GCPS: Graded Chronic Pain Scale.

^b^PROMIS: Patient-Reported Outcomes Measurement Information System.

^c^IMI: Intrinsic Motivation Inventory.

^d^PGIC: Patient Global Impression of Change.

^e^ACS: Attentional Control Scale.

^f^BIS and BAS: Behavioral Inhibition System and Behavioral Activation System Scales.

^g^PCS: Pain Catastrophizing Scale.

#### Baseline Information

At baseline, participants will report on demographic information pertaining to age, gender, first language, country of birth, country of residence, postcode of current home address, ethnicity, marital status, employment status, education level, and hand preference. Participants will also report on the type of computer (eg, laptop), screen size and keyboard (eg, QWERTY) they are using, their health in general, whether they currently have a mental health condition (eg, depression), and on their pain experience information, including current pain problems, formal diagnosis of the pain condition (ie, by a physician), duration of primary pain condition, body locations where they experience pain, area of the body that hurts the most, how the primary pain condition began (eg, postsurgical), current treatment for the pain problem (eg, physiotherapy), and frequency of health care use.

To provide additional information characterizing participants’ overall pain severity, participants will complete the Graded Chronic Pain Scale (GCPS) [50]. The GCPS is a 7-item self-report instrument designed to assess 2 dimensions of chronic pain severity (pain intensity and pain-related disability) in the general population and in primary health care settings. The scale measures the presence of chronic pain in the past 6 months, and all items, except for the number of days disabled, are scored on an 11-point Likert scale, with responses ranging from 0 to 10. Subscale scores (ie, characteristic pain intensity, disability score, and disability points) for the 2 dimensions are combined to calculate a chronic pain grade that allows individuals with chronic pain to be classified into 1 of 5 hierarchical categories: grades 0 (*no pain problem*) to 4 (*high disability-high intensity*). The GCPS has been found to have acceptable to excellent internal consistency, with a Cronbach α ranging from .74 to .91 [50,51]. Dunn et al [52] found that the test–retest reliability after a 2-week interval was good, with a weighted Cohen κ of 0.81.

#### Primary Outcome Measures

##### Pain Intensity

Pain intensity will be assessed using the Patient-Reported Outcomes Measurement Information System (PROMIS) Pain Intensity–Short Form 3a (v1.0; 3 items) [53]. The first 2 items assess pain intensity using a 7-day recall period and are rated on a 5-point Likert scale ranging from 1 (*no pain*) to 5 (*very severe*). The last item asks participants to rate their level of pain *right now* and is rated on a 5-point Likert scale that ranges from 1 (*no pain*) to 5 (*very severe*). Raw score totals are transformed to T-score metrics using the PROMIS conversion tables, such that the average score for the general population is 50 and the SD 10. Higher T-scores represent worse pain. PROMIS Pain Intensity has been shown to be valid for assessing pain in various settings [54].

##### Pain Interference

The impact of pain on daily life will be assessed using the PROMIS Pain Interference–Short Form 8a (version 1.0; 8 items) [53]. The items have a 7-day time frame and are rated on a 5-point Likert scale ranging from 1 (*not at all*) to 5 (*very much*). Raw score totals are transformed to T-score metrics using the PROMIS conversion tables, such that the average score for the general population is 50 and the SD 10. Higher T-scores represent greater pain interference. PROMIS Pain Interference has been assessed and validated in both general and clinical populations [54,55].

##### Engagement

Participants’ experiences of engagement will be assessed using 2 self-report measures. Task-related engagement will be measured after each training session with a single-item question: *How engaging was this session?* The item is rated on a 10-point Likert scale, ranging from 1 (*not at all*) to 10 (*very much*), with a higher score indicating greater engagement. Task-related interest and enjoyment will be assessed using the Intrinsic Motivation Inventory—Interest and Enjoyment subscale [56-58]. The subscale comprises 7 items, which are scored on a 7-point Likert scale ranging from 1 (*not at all*) to 7 (*very true*), with higher scores representing higher levels of interest and enjoyment. The reliability and validity of this subscale have been established in previous research [59,60].

Nonuse intervention attrition [61] (ie, the proportion of participants who discontinue using the intervention at each training session) and completion rates (ie, the proportion of sessions, out of 6, that each participant completes during the training period) will be used as objective behavioral measures of engagement.

#### Secondary Outcome Measures

##### Measure of Attentional Bias for Pain

Attentional biases will be measured using the standard dot-probe paradigm [62]. This task is similar to the one used during the experimental phase, except that the probe replaces each of the words in each pair with equal frequency. Before the assessment blocks, participants will complete a block of 17 practice trials, comprising 16 neutral stimulus pairs and 1 digit trial. Stimuli will be presented in a randomized order across trials and participants, and trials will be intermixed and randomly presented in 2 blocks, with a rest offered between the blocks. Each block will comprise 68 trials (32 [47%] congruent trials; 32 [47%] incongruent trials; 4 [6%] digit trials), totaling 136 trials. Consistent with previous research [10,28], practice trials, digit trials, incorrect trials, and responses <200 milliseconds or >1000 milliseconds will be excluded from the calculation of mean RTs. An attentional bias index will be calculated using the following formula: mean RT of incongruent trials–mean RT of congruent trials. Positive scores will be indicative of an attentional bias toward pain-related stimuli, whereas negative scores will reflect an attentional bias toward neutral stimuli.

##### Anxiety and Depression

Negative affect will be assessed with 2 PROMIS measures comprising PROMIS Anxiety 8a (version 1.0; 8 items) and PROMIS Depression 8b (version 1.0; 8 items) [53]. The items have a 7-day period and are rated on a 5-point Likert scale ranging from 1 (*never*) to 5 (*always*). The raw score totals on each scale will be transformed to T-score metrics using the PROMIS conversion tables, such that the average score for the general population is 50 and the SD 10. Higher T-scores represent greater symptoms of anxiety or depression. The 2 PROMIS measures have demonstrated excellent psychometric properties in both population-based [63] and clinical samples [64,65].

##### Perceived Improvement

Participants’ perception of overall pain-related improvement following training will be assessed using the Patient Global Impression of Change (PGIC) scale [66]. This measure comprises a single item rated on a 7-point Likert scale, ranging from 1 (*very much improved*) to 7 (*very much worse*), with *no change* in the middle of the scale (4). For descriptive purposes, participants will be classified into 3 categories according to the PGIC score: disease deterioration (0-3 points), stable disease (4 points), or disease improvement (5-7 points) since the start of the program [67]. The PGIC has been recommended by the Initiative on Methods, Measurement, and Pain Assessment in Clinical Trials [68] and is widely used in chronic pain research [67,69].

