#### Perceived Improvements

To determine changes in perceived improvement in the different training groups, a multilevel modeling analysis will be conducted. The time point (level 1 units) will be nested within participants (level 2 units). The variable time will have 2 levels (ie, posttraining and 1-month follow-up), with posttraining as the reference point. The control group (control ABMT) will serve as a reference group for comparisons between the groups over time. A model-building procedure [84] will be used to build the most parsimonious model to test the hypothesis, using the AIC to identify the most appropriate model. The model will be computed using maximum likelihood estimation.

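### The protocol contradicts itself on the direction and range of the PGIC: the descriptive categories run opposite to the printed scale and include a score of 0 that cannot occur

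*Protocol article*

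**What the plan says.** Under Secondary Outcome Measures, Perceived Improvement, the protocol article makes three statements about the PGIC score:

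- The item is scored "ranging from 1 (*very much improved*) to 7 (*very much worse".
- The neutral point is central: "with *no change* in the middle of the scale (4".
- A grouping follows: "For descriptive purposes, participants will be classified into 3 categories according to the PGIC score". The groups are "disease deterioration (0-3 points), stable disease (4 points), or disease improvement (5-7 points) since the start of the program", and the grouping is attributed to a cited source.

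Table 1 lists the PGIC as a secondary outcome, measured posttraining and at the 1-month follow-up. Its analysis is given under Statistical Methods, Perceived Improvements: "To determine changes in perceived improvement in the different training groups, a multilevel modeling analysis will be conducted". On timing, that section says: "The variable time will have 2 levels (ie, posttraining and 1-month follow-up), with posttraining as the reference point". The control arm is the reference group. The three categories do not appear there.

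Nowhere does the article say that the PGIC is reverse-scored or recoded.

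**The concern.** On the printed anchors a low score is good and a high score is bad. The printed cut-offs treat a low score as bad and a high score as good. Anyone building the descriptive table from the article would have to break one of the two sentences.

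What is at stake is the descriptive picture of a patient-reported secondary outcome for which the Aims and Hypotheses section makes a directional prediction: more improvement in both active arms than in the sham arm, and most in the gamified arm. If the anchors are right and the cut-offs are used literally, data supporting that prediction would be tabulated as more deterioration in the active arms.

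There is also a question of reading. The article states which direction is better or worse for the PROMIS scales, and what a higher score means for the engagement measures and the Attentional Control Scale. For the PGIC the reader has only the anchors and the cut-offs, and these disagree.

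**Working it through.** The plan gives no figure to reproduce here. The check maps each possible score to its meaning under the anchors and to its category under the cut-offs.

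Inputs, all from Perceived Improvement: 1 is the best end, 7 the worst end, 4 is no change; 0-3 is labelled deterioration, 4 stable, 5-7 improvement. The labels for scores 2, 3, 5 and 6 are not printed, but their side of the scale follows from the two ends and the midpoint.

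| Score s | Meaning under the anchors | Category as printed | Agree? | 8 − s | Category of 8 − s | Agree? |
|---|---|---|---|---|---|---|
| 1 | improved | deterioration | no | 7 | improvement | yes |
| 2 | improved | deterioration | no | 6 | improvement | yes |
| 3 | improved | deterioration | no | 5 | improvement | yes |
| 4 | no change | stable | yes | 4 | stable | yes |
| 5 | worse | improvement | no | 3 | deterioration | yes |
| 6 | worse | improvement | no | 2 | deterioration | yes |
| 7 | worse | improvement | no | 1 | deterioration | yes |

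As printed, 1 of 7 scores agrees and 6 of 7 go to the opposite category. After reverse-scoring, or after swapping the two outer labels, all 7 agree.

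Range: the cut-offs cover 0 to 7, which is 8 values. The item has 7, from 1 to 7. The value 0 cannot be observed, so it misclassifies nobody, but it shows that the cut-offs do not fit the scale as described.

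Effect on the table, if the anchors are right: let p be the proportion improved and w the proportion worse. The literal table reports w as improved and p as deteriorated, so the net difference changes from p − w to w − p. As an illustration only, with assumed proportions of 50% improved, 35% unchanged and 15% worse, the table would show 15% improved and 50% deteriorated, and the net difference would go from +35 to −35 percentage points. The size depends on the split: there is no visible change when p = w, and a full reversal when everyone who changes moves the same way.

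Effect on the model: the cut-offs do not enter it, so nothing in its fit changes. Only the reading of the sign needs a stated direction. Under the printed anchors, a negative difference from control favours training. If the anchors are the misprint, a positive difference does.

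**The case against.** The strongest reply concerns reach. The grouping is explicitly descriptive. No test, sample-size figure or primary outcome uses it, and no responder analysis is planned. The model is specified separately and contains no error of its own. The scores are recorded on the 7-point item, so the table can be regenerated at any time. All of this stands, and it is why the point is of moderate severity.

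A second reply concerns certainty. A reader might infer that every improved participant will be reported as deteriorated. That requires both that the printed anchors match the item in the survey and that the printed labels are applied literally. The document establishes neither. The cut-offs come from a cited source that is not available here, and the impossible 0 does not prove which sentence is wrong. This also stands: the supportable claim is that the sentences conflict.

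A reader might also infer that the PGIC hypothesis test would come out reversed. The document does not support that, because the model does not use the categories and the anchors do give a printed direction. An undefined sign is a reason to state the direction, not evidence that the coefficient will be misread.

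It might finally be said that the coding scheme, which the Data Management and Monitoring section offers on request, will settle the matter. It may, but it does not correct a rule that the article itself states. This is a stated contradiction, not a detail left to another document.

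**Conclusion.** Wrong as written, moderate severity. The Perceived Improvement section contradicts itself on the direction and the range of the PGIC. Read literally, the descriptive summary swaps improved and worsened for every participant not scoring 4, which is 6 of the 7 possible scores. The estimates and P values of the multilevel model, and all primary outcomes, are unaffected.

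The size of the swap in the table rests on two assumptions: that the printed anchors are those administered, and that the cut-offs are applied to the unrecoded score. If the anchors are the misprint, the category labels are right apart from the 0, and the printed direction of the scale is what needs correcting. The contradiction itself rests on neither assumption.

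**What to change.** 1. Check the PGIC item as administered in the Qualtrics survey, including the numeric values stored for each response option. This comes first, because a recode based on the wrong sentence would create the inversion it is meant to remove.
2. If the printed anchors are correct, define improvement as 1-3, stable as 4 and deterioration as 5-7. Equivalently, reverse-score as 8 minus the score, and then apply 1-3 deterioration, 4 stable, 5-7 improvement.
3. If the anchors are the misprint, correct them and keep the category labels.
4. In either case, remove the score 0.
5. State in one phrase whether a higher PGIC score is better or worse, so that the descriptive table and the model coefficients are read the same way.

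The cost is a check of the survey, a corrected sentence or two and at most one recode. Data collection and the planned model do not change.

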##### Measure of Interpretation Bias for Pain

Interpretation bias will be measured using an adapted version of the computerized interpretation bias task [70], which contains 16 vignettes that describe 8 ambiguous situations that may be interpreted as relating to bodily threat or pain and 8 ambiguous social situations. Vignettes were adapted to reflect events that may occur in the workplace, home, or during an adult’s everyday life. Participants will be instructed to imagine themselves in the situation, and after reading each ambiguous scenario, they will be offered end words that resolve the situation in a benign or negative manner. Participants will then rate whether each resolution came to their mind on a scale of 1 (*does not pop into my mind*) to 5 (*definitely pops into my mind*) and select the interpretation (word) that most easily popped into their head. Next, participants will be presented with the same scenarios again; however, this time, they will be asked to rate the likelihood that each resolution would actually happen in that situation on a scale of 1 (*not likely*) to 5 (*very likely*). Finally, participants will select the word that they believe is most likely to end the sentence. All items and interpretations will be presented in a fixed random order to ensure all participants view the same order of items and response choices. Studies using this task have found evidence of interpretation bias in relation to pain in individuals with chronic pain [71].

#### Additional Measures

##### Measure of Attentional Control

Attentional control will be assessed using the Attentional Control Scale (ACS). The ACS [72] is a 20-item self-report questionnaire used to measure attention focusing and attention shifting. The questionnaire is adapted by including a 7-day time frame for the items. Items are scored on a 4-point Likert scale from 1 (*almost never*) to 4 (*always*), with scores ranging from 20 to 80. Higher scores indicate a better ability to direct and maintain attention. The ACS has been found to have good reliability, with a Cronbach α of .81 [10] and good concurrent validity [72].

##### Personality Characteristics

Personality traits will be measured using the Behavioral Inhibition System (BIS) and Behavioral Activation System (BAS) scales [73], a 20-item self-report questionnaire that measures trait sensitivity levels of the BIS (punishment; 7 items) and BAS (reward; 13 items). The scales are scored on a 4-point Likert scale ranging from 1 (*strongly disagree*) to 4 (*strongly agree*). Meyer et al [74] found that internal consistency ranged from acceptable to good for the BIS and BAS scales. Test–retest reliability over 2 months was acceptable for both scales [73].

##### Pain-Related Worrying

Participants’ pain-related worrying [75] will be assessed using the Pain Catastrophizing Scale (PCS) [76]. The PCS is a 13-item self-report measure that evaluates 3 subscales: rumination, magnification, and helplessness. Using a 5-point Likert scale, ranging from 0 (*not at all*) to 4 (*all the time*), participants will be asked to recall past painful experiences and indicate the extent to which 13 thoughts or feelings are associated with these experiences. The 3 subscale scores are summed to provide a total score for pain catastrophizing, which ranges from 0 (*low degree of catastrophizing*) to 52 (*high degree of catastrophizing*). The PCS has been found to have good validity and reliability for individuals with chronic pain [76,77].

##### Pain-Treatment Information

At the posttraining and 1-month follow-up assessments, there will be a question that probes participants’ pain treatments and frequency of health care use since the commencement of the study or previous assessment.

##### Manipulation Check

At the posttraining assessment, there will be a manipulation check question asking participants which training condition they believe they had received (ABMT or sham training).

##### Validity Check

As recommended by Oppenheimer et al [78], instructional questions will be included in the pre- and posttraining surveys (eg, please select *5=Always*) to identify careless responding patterns. Participants will be excluded if they answer all instructional questions incorrectly.

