### Randomization, Allocation Concealment, and Blinding

Participants fulfilling eligibility criteria and willing to participate in this study will be randomly allocated to 1 of the 3 training conditions after the baseline assessment. Randomization will be performed before participants are enrolled by an independent person blinded to all processes within the intervention, using a computerized random number generator. A block randomization technique will be used, allowing 6 participants at a time to be randomized in equal proportions to the 3 training arms. The allocation numbers will be stored on a password-protected university database maintained by the same independent person and will be revealed after participants are enrolled and baseline assessments are completed.

Each time a participant completes the baseline survey, an automatic email will be sent to the principal researcher ([name]). After receiving this email, the participant will be allocated to the next number on the list and, consequently, be assigned to a training arm. Researchers and participants will be blinded to group allocation throughout the trial (ie, double-blind study design). Furthermore, as assessments and training will occur on the web, in the absence of the investigators, the outcome data will be blinded. However, it is possible that a researcher could become aware of the participants’ training conditions to support them adequately in the instance of technical problems. However, it is unlikely that this will entail problems of bias allocation or assessment because of the web-based nature of the study.

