### Statistical Methods

#### Overview

Statistical analyses will be conducted after data collection is completed using the SPSS version 27.0 or later (IBM Corp). Continuous data will be presented as means and SDs, whereas categorical data will be presented as frequencies and percentages. Analyses will follow the intention-to-treat principle and will include all randomized participants who successfully complete at least one training session (ie, minimum threshold exposure to ABMT). To determine whether there are any pretraining differences between the training conditions on demographic variables and baseline characteristics, a series of analyses will be performed. The rates of and reasons for missing data will be reported. To manage missing data, the study will attempt to follow-up on all randomized participants (even if they withdraw from the trial) and, where appropriate, use multilevel modeling for repeated measure data analyses as it allows the incorporation of all available data. Significance for all statistical tests will be set at *P*<.05 (2-tailed). Effect sizes will be presented by its most appropriate effect size (and 95% CI), as described by Lakens [82], with a preference for Cohen *d* where possible [83]. No interim analyses of the trial outcome data are planned.

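### The attention-check exclusion is settled only after randomisation and training, and it contradicts the analysis set that the protocol calls intention-to-treat

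*Protocol article*

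**What the plan says.** **The rule.** In the protocol article, Validity Check, "instructional questions will be included in the pre- and posttraining surveys" to detect careless responding. The consequence is: "Participants will be excluded if they answer all instructional questions incorrectly". No time point and no particular analysis is attached to the exclusion.

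**Where the checks sit.** Table 1, under Additional measures, lists "Validity check" and ticks it at baseline, posttraining and 1-month follow-up. That is one survey more than the Validity Check text names.

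**When allocation happens.** The section on randomisation says participants "will be randomly allocated to 1 of the 3 training conditions after the baseline assessment". It adds: "Each time a participant completes the baseline survey, an automatic email will be sent to the principal researcher". The next number on the list is then assigned. No look at the instructional answers is described between survey and allocation.

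**Who is analysed.** Statistical Methods, Overview: "Analyses will follow the intention-to-treat principle and will include all randomized participants who successfully complete at least one training session". No exception is made for failed checks.

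**Who sees the later checks.** Under Procedure, the invitation to the posttraining survey comes on completion of the final session. The Statistical Methods overview also says that follow-up of everyone randomised, including those who withdraw, will be attempted.

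**The concern.** Two stated rules define two different primary populations. A randomised participant who completes a session and answers every check wrongly is removed by one and retained by the other.

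The removing rule also cannot be completed at baseline. Its condition covers all the checks, and some are put only after training. Whether a person who failed at baseline is finally removed therefore depends on whether that person reached and returned a later survey. Attrition and sessions completed are primary outcomes (Engagement; Engagement Measures), compared by log-rank test and analysis of variance. Membership of the analysis set would then depend on something close to the outcome itself. The trial's hypothesis is that gamification changes engagement, so the chance of reaching, and attending to, a later check could differ by arm.

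**Working it through.** The protocol gives no figure here to reproduce. The check has two parts: reading the sections against each other, and illustrating the possible size.

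**Step 1. The contradiction.** Take a participant who is randomised, completes session 1 and answers every check wrongly. Validity Check excludes this person; Statistical Methods, Overview includes this person. Neither section defers to the other.

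**Step 2. What later answers can do.** Exclusion needs all answers to be wrong, and the baseline items are among them. A wrong posttraining answer alone excludes nobody who answered a baseline item correctly. A correct later answer can only rescue someone who failed at baseline. The post-randomisation part of the rule is this rescue step, and it is capped by the baseline failure rate.

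**Step 3. Missing later surveys.** Two readings are open.

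- Reading A: only answered questions count, or unanswered counts as wrong. A dropout who failed at baseline is removed; a completer who failed at baseline is removed only if the later checks are failed too.
- Reading B: an unanswered question is not an incorrect answer. Dropouts without later surveys are never removed; completers can be.

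**Step 4. Size.** Inputs from the protocol (Sample Size Estimation): 40 per arm and about 30% dropout. Assumed, because the protocol gives no figures:

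- f, the probability of failing all baseline checks: 2% to 20%;
- c, the probability that a completer who failed at baseline fails all later checks: 0.1 to 0.8;
- true attrition d: 30% in every arm, or 20% gamified against 40% control.

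Dropouts are taken to return no later survey.

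Reading A: observed attrition = d(1 − f) / [d(1 − f) + (1 − d)(1 − fc)].

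Example with d = 0.30, f = 0.05, c = 0.3: 0.285 / (0.285 + 0.6895) = 29.2%. Removals per arm: 40 × 0.30 × 0.05 = 0.60 dropouts, plus 40 × 0.70 × 0.015 = 0.42 completers, about 1 of 40.

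| f, c | True 30% seen as | True 20-point difference seen as |
|---|---|---|
| 5%, 0.3 | 29.2% | 19.7 |
| 10%, 0.3 | 28.5% | 19.4 |
| 20%, 0.1 | 25.9% | 18.3 |

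At the mild end (f = 2%, c = 0.8) the difference stays at 20.0. A dropout is 1/c times as likely to be removed as a completer: 1.25 times at c = 0.8, 10 times at c = 0.1.

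Variations on Reading A:

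- Dropouts fail baseline checks twice as often as completers (c = 0.3): the 20-point difference is seen as 19.3, 18.4 and 16.1 for completer f of 5%, 10% and 20%.
- Equal attrition, f and c in all arms: no between-arm bias.
- Equal attrition of 30%, but c = 0.1 gamified and 0.5 control: a false difference of 0.4, 0.8 and 1.7 points for f = 5%, 10% and 20%.

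Reading B: observed attrition = d / [d + (1 − d)(1 − fc)]. For f from 5% to 20% and c of 0.3 or 0.5, 30% is seen as 30.3% to 32.3%, and the 20-point difference as 20.1 to 20.8. The direction reverses.

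**Step 5. With nobody removed.** Observed attrition equals true attrition, and the difference is 20.0 points.

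**The case against.** The strongest reply is that this is a wording inconsistency with little practical effect. Requiring every answer to be wrong is lenient and removes few people, which favours intention-to-treat. An early dropout with no later survey would be judged, if at all, on answers given before randomisation. Follow-up of withdrawals is planned, so some dropouts may still return later checks. The treatment of unanswered items can properly be left to the full protocol or analysis plan, which are not shown.

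Most of this stands, and it rules out three stronger readings that a reader might infer.

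- That posttraining answers by themselves get people excluded. The word all includes the baseline items, so later answers can only rescue.
- That the rule hits early dropouts hardest. This follows under Reading A and reverses under Reading B; the text does not choose.
- That the same careless behaviour is about 1.6 to 2.4 times as likely to exclude someone who leaves early. This assumes one or two five-option items per survey, purely random answering (0.8 raised to the number of items answered) and the three surveys of Table 1: 0.80/0.51 and 0.64/0.26. With the two surveys named under Validity Check it is 0.80/0.64 = 1.25 and 0.64/0.41 = 1.6. The protocol does not state the number of items per survey, and the ratio says nothing about how many such responders there are.

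The reply does not remove the conflict itself. The article does not leave the analysis set open: it states two rules that cannot both be followed.

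**Conclusion.** The point holds in a limited form. The exclusion can be completed only after randomisation and training, it contradicts the stated intention-to-treat set, and under either reading it makes removal depend on how far a participant got. The Validity Check text and Table 1 also disagree on which surveys count.

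Bias in the engagement outcomes is a risk and has not been shown. Under the assumed ranges, Reading A mostly dilutes a true 20-point attrition difference by 0 to 2 points, or by about 4 if dropouts also fail the baseline checks twice as often and f is 20%. A false difference needs failure of the later checks to vary by arm, and is then 0.4 to 1.7 points in the cases tried. Reading B inflates the difference by less than 1 point. All these sizes rest on assumed values of f, c and attrition by arm. The contradiction rests on the text alone. It matters chiefly because the choice of population could otherwise be made after the data are seen.

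**What to change.** State in Validity Check and in Statistical Methods, Overview that every randomised participant with at least one completed session stays in the primary analyses, whatever the answers to the instructional questions. Use failed checks only in a prespecified sensitivity analysis, for example by setting to missing the scores from the survey in which the checks were failed. Make Validity Check and Table 1 agree on which surveys carry the questions.

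The cost is a few sentences, to be settled before analysis. The downside is that a few careless responses remain in the main analysis; the sensitivity analysis shows whether they matter.

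Screening on the baseline items before allocation would also avoid a post-randomisation exclusion. However, recruitment began in August 2021 and was ongoing when the article was written (Results), so it could not reach those already randomised and would add an entry criterion during the trial. The wording change covers everyone.
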